### Data analysis

Data from the PEP++ trial will be analysed primarily through quantitative methods using descriptive analysis for all variables. Table 3 outlines the tools to be used to measure and analyse the study outcomes.

**Table 3 Tab3:** PEP++ project outcomes and statistical analysis plan

Objective	Outcome	Hypothesis	Outcome measure	Method of analysis
To provide evidence of the effectiveness of an enhanced post-exposure prophylaxis regimen (PEP++) compared to SDR-PEP	Primary: contacts diagnosed with leprosy	PEP++ offers a higher protection against leprosy disease manifestation than SDR-PEP	Number of persons with leprosy disease detected at 24 months after receiving prophylaxis	Descriptive statistics; Cox’ proportion hazards analysis and Poisson regression comparing rates between the intervention and control areas
To show the cost- benefit and acceptability of the enhanced chemoprophylaxis regimen	Secondary: Cost–benefit of the enhanced regimen compared with effectiveness of SDR-PEP	PEP++ is a cost-effective strategy in leprosy control and the increased effectiveness of the intervention will justify additional costs from multiple doses	Number of contacts screened, cases prevented, and disabilities avoided against operational costs and out-of-pocket expenses	Health economic evaluation
	Secondary: Acceptability of the enhanced regimen compared with SDR-PEP	The new regimen will be accepted by contacts and health professionals	Proportion of eligible close contacts who take all three doses; qualitative interview results indicating that PEP++ is acceptable	Descriptive statistics of contacts who took medication; qualitative content analysis of interviews; semi-structured interviews, FGDs
To provide evidence of increased transmission of *M. leprae* in cluster areas identified through GIS-based mapping compared to non-cluster areas	Secondary: Contacts diagnosed with leprosy in identified high-transmission clusters (2014–19 index cases)	Detection of new leprosy cases will be higher in the cluster areas than in non-cluster areas due to higher local transmission and relative risk	Rate ratios of all new leprosy cases and child cases in cluster areas as compared with non-cluster areas (as a result of intervention as well as passive cases); rate ratio	Poisson regression comparing rates between cluster and non-cluster areas
To demonstrate the effectiveness of the community education and behaviour change interventions to change the perception of leprosy in the study districts	Secondary: Levels of knowledge, attitudes, and stigma in each district	New, contextualised education materials and interventions will increase community knowledge regarding leprosy and reduce stigma so as to promote early detection	Change in KAP, EMIC-CSS and SDS scores and interviews/FGDs in all four target groups	Descriptive statistics; comparison of mean/median scores between baseline and end-line surveys; effect size; correlations between exposure to the interventions and KAP, EMIC-CSS and SDS scores; multivariate regression; qualitative content analysis of interviews, FGDs, and observations
To demonstrate proof of concept of the potential for the PEP++ approach to reduce, and ultimately stop, the transmission of *M. leprae* in a target area	Primary: Detection of new autochthonous child cases of leprosy	Reduction in new case and child case detection will be higher in intervention compared with control areas; Overall and child case detection levels will reduce against baseline (2019) detection	Rate ratio of new case and child case detection per 1,000,000 population; total number of new cases per district	Descriptive statistics, comparison of new case and child case detection rates between the intervention and control areas

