### Leprosy perception

A person’s perception of leprosy can negatively affect health-seeking behaviour and the acceptance of new interventions [16]. Therefore, contextualised community education and behaviour change (CEBC) materials are developed as part of the study to change the perception (knowledge, attitudes, beliefs, and emotions) regarding leprosy and reduce stigma, as well as to increase the community acceptance of preventive treatment. First, a leprosy perception study was conducted in each country to investigate the perceptions of leprosy patients, contacts, community members and health workers regarding leprosy, i.e., the way people see leprosy, what they know about leprosy and their attitudes, beliefs and reported behaviour towards persons affected by leprosy [17, 18]. A mixed-method approach will be used to measure the perception, including in-depth interviews, focus group discussions (FGDs), the knowledge, attitudes, and practices (KAP) tool, the Explanatory Model Interview Catalogue Community Stigma Scale (EMIC-CSS) and the Social Distance Scale (SDS). During a workshop, leprosy affected persons and other key stakeholders will use the outcomes of the perception study to develop messages for the CEBC materials. The CEBC materials will be distributed throughout the implementation areas and piloted before the start of the trial [19].

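### The CEBC objective claims demonstrated effectiveness from an uncontrolled before-after comparison that is confounded with time trend and the trial's own activity

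*Protocol article*

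**What the plan says.** The CEBC row of Table 3 (Data analysis) states its objective as "To demonstrate the effectiveness of the community education and behaviour change interventions to change the perception of leprosy in the study districts". Its hypothesis is that new materials "will increase community knowledge regarding leprosy and reduce stigma so as to promote early detection". The outcome measure is "Change in KAP, EMIC-CSS and SDS scores and interviews/FGDs in all four target groups". The methods cell lists descriptive statistics, "comparison of mean/median scores between baseline and end-line surveys", an effect size, correlations of exposure with the three scores, multivariate regression, and qualitative analysis. The Objectives section also lists the effectiveness of CEBC among the things to be evidenced.

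The section Leprosy perception appears to identify the four groups. It describes a study of the "perceptions of leprosy patients, contacts, community members and health workers regarding leprosy", already carried out in each country. On delivery it says: "The CEBC materials will be distributed throughout the implementation areas and piloted before the start of the trial".

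**The concern.** The objective is causal, but the leading quantitative comparison has no concurrent control for CEBC. Two other things happen over the same period: perceptions may drift for reasons outside the project, and the trial itself brings staff, information, screening and medication to many of the people whose views are surveyed. If scores improve, the plan as written would allow the improvement to be credited to the education materials. That conclusion could then be used to recommend the materials elsewhere without the visits that accompanied them here.

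**Working it through.** The article states no sample size, standard deviation, effect size or power for this endpoint. The Sample size section deals only with leprosy detection rates. There is thus no figure to reproduce, and the check sets the relevant sections side by side.

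1. **What is randomised.** Under Study design, sub-districts are allocated to PEP++ or SDR-PEP. CEBC is not part of the allocation.

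2. **Where CEBC goes.** Under Leprosy perception, it goes to all implementation areas. No CEBC-free or delayed area is described, so neither the randomised arms nor any other geographic contrast in the article isolates CEBC.

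3. **What else reaches the surveyed groups.**
   - Contacts: Participants says that all contacts who are listed and located are enrolled and informed about the study. Data collection adds home visits and consent. Study design adds screening and the regimen.
   - Community members: Blanket campaigns says that people living near index cases in clusters are visited, asked for consent, screened and, if eligible, given SDR-PEP.
   - Leprosy patients: Participants says that index cases are approached, asked for consent and asked to list contacts.

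4. **When.** The perception study preceded the development of the materials, which were to be piloted before the trial began. If it supplied the baseline, as seems likely, trial activity falls between the surveys unless end-line came before intake. The text does not date end-line; the study schedule figure may.

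5. **What the before-after change contains.** For target group g, write

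   observed change(g) = CEBC effect(g) + secular trend(g) + effect of trial activity(g).

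   There is one observed quantity and three unknowns. The first term is recovered only if the other two are zero or can be estimated elsewhere. A CEBC-free area would supply the second; a record of who was enrolled would help with the third. The article describes neither for this endpoint. The third term is probably largest in contacts, since nearly all are meant to be visited, and reaches community members only in part.

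6. **What the exposure analysis adds.** It compares more exposed with less exposed respondents and so does not rest on calendar time alone. It isolates CEBC only if exposure is unrelated to enrolment in the trial and to prior interest in leprosy. People visited by study staff may well have seen more of the materials, and the article does not say that enrolment enters the regression.

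**The case against.** The best defence is that effectiveness is not read from the before-after change alone. The same table cell plans exposure correlations, multivariate regression and qualitative work. That stands, and it rules out saying that the plan can show nothing about CEBC. It does not rescue the causal wording, because the exposure contrast is observational and may be entangled with trial visits.

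Three stronger readings are tempting, and the article does not support them:

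- *Surveying patients and contacts is what breaks the inference.* The objective covers perception in the districts, so these groups belong in it. Community members are already a separate group, and limiting the endpoint to them would still leave no control. It would also leave blanket campaigns reaching some of them unless those people were excluded.
- *The four groups are averaged, so a gain in contacts inflates a pooled result.* Nothing says that they are pooled. The wording reads naturally as change measured in each group, and any figure for pooled inflation would rest on invented inputs.
- *The community stigma and social distance scales lose their meaning in patients.* The article does not say which instrument each group completes and shows no items or scoring. A condensed article may leave that to the full protocol.

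It is also fair to object that the article says only contacts, not enrolled contacts. That surveyed contacts will largely be trial participants is an inference, although a strong one: all eligible patients in the districts are asked to list contacts, and all contacts who are located are enrolled.

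**Conclusion.** The point holds as a mismatch between claim and design. The CEBC comparison has no concurrent control and is confounded with secular trend and with the trial's own activity, most clearly among contacts. The planned exposure analysis reduces this but does not remove it, so the plan supports statements of change and association, not of demonstrated effectiveness.

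The size of the bias cannot be given from the article. The conclusion assumes that end-line follows at least part of the intake, that the contacts surveyed are mostly those whom the trial enrols, and that no CEBC-free area exists beyond what the article describes. The importance is minor: this is a secondary endpoint, and the randomised regimen comparison does not depend on it.

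**What to change.** 1. In the Table 3 CEBC row, state that the change is reported separately for each of the four target groups.
2. Add one end-line question: whether the respondent was enrolled in PEP++ as a close or a blanket contact.
3. Use the answer as a covariate or stratifier in the exposure correlations and multivariate regression already planned, and show the result among unenrolled community members.
4. Reword the objective, both in Table 3 and under Objectives, and the conclusion as change over the project period and association with CEBC exposure.

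If the full protocol contains a CEBC-free or delayed area, name it and make that the comparison; stronger wording could then be reconsidered.

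The costs are one survey item, smaller strata with less precise estimates, and a more modest claim. The steps deal with overlap between exposure and trial visits; they do not remove secular trend, which is why the rewording is needed as well. Dropping scales for patients, or confining the endpoint to unenrolled community members, is a matter of preference and is not required.

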## Background

Leprosy, or Hansen’s disease, is an infectious disease caused by *Mycobacterium leprae* [1]. Although the transmission is not fully understood, the main mode is human-to-human via respiratory aerosols through coughing and sneezing. Prolonged and frequent close contact with an infectious person who has not started treatment is necessary for transmission [1, 2]. Therefore, individuals living in the same household as a person affected by the disease, neighbours and other family members are at a higher risk of being infected [2].

In 2022, the number of new leprosy patients reported globally was 174,087. The majority of the world’s leprosy patients (78%) live in three countries: India (60%), Brazil (11%) and Indonesia (7%). An additional 17% come from the next 20 global priority countries, including Bangladesh and Nepal [3]. Between 2010 and 2019, the annual decrease in new leprosy cases globally was a modest 2% per year [4]. Therefore, new interventions, such as more precise active case finding and chemoprophylaxis, are essential to reduce the global caseload.

Trials to study the effectiveness of chemoprophylaxis to prevent leprosy have been conducted for decades. The first successful leprosy chemoprophylaxis trials were conducted with dapsone administered weekly or biweekly for months or years with limited effectiveness [5]. More research was required for more powerful single dose regimens. Rifampicin (RMP), recognised as the most effective bactericidal agent against *M*. *leprae*, was subsequently researched [6]. A single dose of rifampicin as leprosy post-exposure prophylaxis (SDR-PEP) was administered to close contacts of leprosy patients to prevent the disease in several studies [7–9].

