### Sample size

The calculation of the sample size is based on the primary objective to find differences in new case detection rates (NCDR). The first is a difference in NCDR in the population in the intervention area after four years, compared to the baseline rate in 2019. The year 2019 is selected as the baseline to avoid any effect of the COVID-19 pandemic. The second is the difference in incidence rates in the contact groups between the close contacts who have received PEP++ and controls who have received SDR-PEP.

The sample size calculation for the difference in rates in the close contacts is based on the NCDR found in contacts in the COLEP trial sample. The NCDR in the SDR intervention group was 291/100,000 over 2 years, or an annual rate of 146/100,000. To reduce this rate by 50%, using a power of 90%, a significance level of 0.05, design effect of 1.5, correction for non-eligibility of 25% and loss to follow-up of 25%, we aimed to enrol 202,360 close contacts. This should result in giving PEP to at least 162,000 participants.

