### Outcome measures

The primary outcome measures of the trial will be the number of new leprosy cases detected, the number of child cases detected, and the incidence rate ratios of each arm compared with 2019 baseline. These will be measured at the two-year follow-up of the trial. In addition, the cost-effectiveness and acceptability of PEP++ as a preventive intervention will be measured as separate side studies. The added value of geospatial methods will be measured by the proportion of new leprosy cases in clusters and non-clusters.

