### Blanket campaigns

As predicted by mathematical modelling, a larger reduction in new cases detected can be achieved by implementing additional blanket campaigns in the identified clusters. For each index case in a cluster, the households not listed as close (neighbour) contacts within a radius of approximately 100 m will be visited until 80 to 100 participants (blanket contacts) are included in the study. If this results in over 80% of the cluster area being covered, then the entire population will be invited for participation. These blanket contacts are, similar to the close contacts, asked for consent to participate in the trial, screened for signs and symptoms of leprosy and when eligible, are provided SDR-PEP.

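### The population-level comparison with 2019 has primary status but cannot show what PEP++ adds to SDR-PEP; inference should rest on the between-arm comparison that Table 3 already names

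*Protocol article*

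**What the plan says.** Three places in the protocol article set up a comparison with 2019.

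- **Sample size** bases the calculation on two differences. "The first is a difference in NCDR in the population in the intervention area after four years, compared to the baseline rate in 2019"; no control area enters this one. The second is the between-arm difference in close contacts. The calculation shown covers only the second.
- **Outcome measures** lists among the primary outcomes "the incidence rate ratios of each arm compared with 2019 baseline".
- **Data analysis, Table 3, last row** (labelled primary) holds two hypotheses. The first is between arms: "Reduction in new case and child case detection will be higher in intervention compared with control areas". The second is before-after: "Overall and child case detection levels will reduce against baseline (2019) detection". Apart from descriptive statistics, the row's method column gives only "comparison of new case and child case detection rates between the intervention and control areas".

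The reason given for the reference year is the pandemic: "The year 2019 is selected as the baseline to avoid any effect of the COVID-19 pandemic". On background trend, the Background section reports that "the annual decrease in new leprosy cases globally was a modest 2% per year" (2010 to 2019). Study activity also changes case finding. Contacts are screened at intake and again two years after the last dose, and blanket contacts are "screened for signs and symptoms of leprosy and when eligible, are provided SDR-PEP".

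**The concern.** Only the comparison between arms is protected by randomisation. A comparison of either arm with 2019 mixes the regimen with everything else that changed.

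- **Pushing detection down:** the background trend, the SDR-level protection that both arms receive, and the SDR-PEP blanket campaigns.
- **Pushing detection up while it takes place:** active screening at intake, at two years and in the campaigns, and community education meant to bring cases forward.

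Choosing 2019 keeps the pandemic out of the reference year but deals with none of these. A fall since 2019 could be credited to the enhanced regimen when it is trend or SDR, and a rise produced by screening could be read as failure. Because the comparison has primary status, either error would reach the trial's main conclusions.

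**Working it through.** **Inputs from the protocol article**
- Contact rate under SDR-PEP: 291 per 100,000 over two years, so 145.5 a year (the article rounds to 146). Planned further reduction: 50%, to 72.75 a year (Sample size).
- SDR-PEP against no PEP: 57% reduction in the first two years (Background).
- Enrolment 202,360; at least 162,000 given PEP (Sample size).
- 14,532 new cases in the study districts, 2015–2020 (Table 1).
- Global decline of 2% a year (Background).

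**Assumptions:** contacts and caseload split equally between arms; the mean of 2015–2020 stands in for 2019, since yearly counts are not given; no PEP in these areas in 2019; no effect through reduced transmission; the global trend holds locally.

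**1. The plan's own figure.** Pooled-variance two-proportion formula, 0.00146 against 0.00073, two-sided 5%, power 90%: 43,132 per arm. Then 43,132 × 2 × 1.5 = 129,396; × 1.25 = 161,745 (stated: 162,000); × 1.25 = 202,181 (stated: 202,360). The stated sizes are reproduced, so 162,000 / 2 = 81,000 treated per arm is a fair basis.

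**2. Yearly detection per arm.** 14,532 / 6 = 2,422; / 2 = 1,211.

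**3. Trend.** 1 − 0.98⁴ = 7.8%, or 94 of 1,211 cases a year. The article does not say from when the four years run; five years give 9.6% and six give 11.4%. If the local decline were 1% or 3% a year, four years would give 3.9% or 11.5%.

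**4. Direct effect of PEP++ on one arm's detection**

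| Contrast | Cases prevented per year | Share of 1,211 |
|---|---|---|
| PEP++ over SDR-PEP, planned 50% | 81,000 × (145.5 − 72.75)/100,000 = 58.9 | 4.9% |
| SDR-PEP over no PEP | 81,000 × (338.4 − 145.5)/100,000 = 156.2 | 12.9% |
| PEP++ over no PEP | 58.9 + 156.2 = 215.2 (before rounding) | 17.8% |
| Ceiling over SDR-PEP (every case prevented) | 81,000 × 145.5/100,000 = 117.9 | 9.7% |

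Here 338.4 = 145.5 / (1 − 0.57). If instead 25% of those enrolled are not treated, 202,360 × 0.75 / 2 = 75,885 per arm, and the planned gain (at the article's rounded 73 per 100,000) is 55.4 cases, or 4.6%.

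Of the modelled fall since 2019, 156.2 / 215.2 = 73% is SDR-level protection that the control arm shares.

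**5. Screening.** At the design rates, contacts develop 81,000 × 0.00291 = 236 cases over two years in the SDR-PEP arm and 118 in the PEP++ arm. That is 19.5% and 9.7% of one year's arm caseload. These are upper limits for net added detection, because some cases would have been found passively and some contacts will be lost. With 25% lost from 75,885 per arm, 56,914 × (0.00291 + 0.001455) = 248 in both arms together. Intake yield is not given. At an assumed 50 to 300 per 100,000, 101,180 contacts per arm give 51 to 304 cases, or 4% to 25% of a year's arm caseload.

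**6. Power of the between-arm population contrast.** Two years of control-arm cases: 2 × 1,211 = 2,422. Design effect 1.5, borrowed from the contact-level calculation. For a rate ratio of 0.954 (the 4.6% gain): SE of the log ratio = √(1.5 × (1/2,422 + 1/(2,422 × 0.954))) = 0.0356; z = 0.0471 / 0.0356 = 1.32; power = Φ(1.32 − 1.96) = 26%. For 0.951 (the 4.9% gain) it is 29%.

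**The case against.** **The trend is not larger than everything PEP++ could do.** A reader might infer that the cited decline outweighs even the largest direct effect of PEP++. The figures do not support that. Against a 2019 without PEP, the modelled effect is 17.8%, more than twice the 7.8% trend, and the ceiling over SDR-PEP is 9.7%. The trend exceeds only the planned gain over SDR-PEP, and only if the local decline is more than about 1.2% a year, since 1 − (1 − 0.049)^(1/4) = 1.2%.

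**The row already contains the randomised comparison.** This is correct. Its first hypothesis and its method column are between arms, and shared trend and shared screening largely cancel there. It would be wrong to say that the plan lacks a controlled population-level comparison. The difficulty is that Sample size and Outcome measures raise the 2019 comparison to primary standing alongside it.

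**The row tests a package, not a regimen.** It aims at proof of concept for the PEP++ approach, and the Discussion combines the regimen with blanket campaigns, so a fall due to SDR-PEP is part of what is studied. This stands in part: a package claim need not separate regimen from campaign. But trend and added case finding are not part of a preventive effect, and they confound a claim about the package too.

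**Pandemic and detail.** The article does not show that the comparison year was affected by the pandemic, so that is not claimed. Adjustment details may sit in an analysis plan that is not shown. The status given to the 2019 contrast, however, is fixed in this document.

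**Conclusion.** The point holds for the 2019 comparison only. As placed in Sample size and Outcome measures, and repeated in Table 3, it cannot show the effect of PEP++ over SDR-PEP. The background decline (about 7.8% over four years) is larger than the planned gain (4.6% to 4.9% of arm-level detection). About 73% of the modelled direct fall since 2019 would be protection that the control arm also receives. Screening acts in the opposite direction, by an amount that could match the effect sought.

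These sizes rest on the assumptions listed above, chiefly the equal split, no PEP in 2019, no transmission effect and a local trend equal to the global one. The conclusion does not depend on the exact values, because an uncontrolled contrast cannot separate these influences at any of them. The randomised contact-level comparison at 24 months, which carries the regimen question, is not affected.

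**What to change.** Reconcile Sample size, Outcome measures and the last row of Table 3.

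1. Rest population-level inference on the randomised rate ratio: Poisson regression of sub-district case counts on arm, allowing for clustering, with each sub-district's pre-trial detection rate as covariate. Case data for 2015–2020 were already used to stratify the randomisation.
2. Show routinely detected and study-screened cases separately.
3. Report the change from 2019 in each arm descriptively only, and remove it from the primary outcomes and from the basis of the sample size.
4. Present the population-level contrast as support for the contact-level primary comparison.

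The cost is mainly wording, plus recording how each case was found. The trial gives up a stand-alone claim of reduction since 2019. The contrast that replaces it has low power for the direct effect alone: about 26% to 29% over two years at an assumed design effect of 1.5. A transmission effect would raise that, and a larger design effect for population counts would lower it.
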